**Fig. 1 Fig1:**
[figure not shown]
Screening process for patient eligibility for enrolment in the UROPOT study

### Trial design

UROPOT is a monocentric randomized double-blinded phase I/II exploratory trial that aims to assess mannitol-potentiated low-dose amikacin’s performance compared to gold standard prophylactic regimens in 90 patients over a 2-year enrolment period. Patients will be randomly assigned to one of three treatment arms (1:1:1 ratio; Fig. 1).

## Methods: participants, interventions, and outcomes

### Study setting

This single-center trial will take place at the Urology Department of the University Hospital of Lausanne, a tertiary university care center in Lausanne, Switzerland.

### Participants/eligibility criteria

Patients with asymptomatic *E. coli* and/or *K. pneumoniae* bacteriuria, undergoing endourological procedures. Inclusion and exclusion criteria determining the eligibility of study participants are reported in Table 1. Bacteriuria is defined as ≥ 10^2^ CFU/ml for both *E. coli* and *K. pneumoniae*. In case of mixed cultures, *E. coli* and/or *K. pneumoniae* should be significantly more enriched than other bacteria (i.e., ratios of quantitative results in CFU/ml of *E. coli*/other bacteria or *K. pneumoniae*/other bacteria are > 100).

**Table 1 Tab1:** Inclusion and exclusion criteria of the UROPOT trial

Participants fulfilling all the following inclusion criteria are eligible for the study:
1. Written informed consent
2. Adults (≥18 years)
3. Patients with a ureteral stent in situ
4. Patients scheduled for endourological ureteral manipulations (e.g. endourological stone surgery, ureteral stent exchange)
5. Asymptomatic bacteriuria with strains of E. coli and/or K. pneumoniae sensitive to ceftriaxone and amikacin.
The presence of any one of the following exclusion criteria will lead to exclusion of the participant:
1. Allergy to one of the study drugs or excipients (Beta-lactams, aminoglycosides or mannitol)
2. Pregnant and lactating women
3. Glomerular filtration rate (CKD-EPI eGFR) < 50ml/min / 1,73m2
4. Middle to severe hearing impairment
5. Myasthenia gravis or other forms of myoneural disorders
6. Congestive heart failure, pulmonary oedema
7. Intracranial haemorrhage, compromised blood-brain barrier
8. Antibiotic treatment within 14 days prior to randomization
9. Mixed cultures of E. coli and/or K. pneumonia with other bacteria
10. Previous (within 3 months prior to randomization) or concomitant participation in another interventional clinical trial
11. Inability to understand and follow the protocol
12. Inability to give informed consent

### Who will take consent

Informed consent will be taken by the medical team (KS, FC, PB) or the study nurse as authorized surrogate (AM). Informed consent (supplementary data) will be sent by mail based on screening cultures and consent will be confirmed on visit 1 (see Table 2).

**Table 2 Tab2:** Study visits

Time before/after day 0 (allocation)	− 30 days (± 15 days)	− 10 days (± 7 days)	− 5 days (± 4 days)	Day 0	Day 2 (± 24 h)	Day 14 (± 4 days)
**Visits**	**Pre-screening**	**Screening/information visit 0**	**Phone contact**	**Visit 1**	**Visit 2**	**Visit 3**
Assessment of potentially eligible patients	x					
**Assessment of eligibility during standard clinical consultation:**						
Inclusion/exclusion criteria check		x		x		
Participant information and delivery of informed consent		x				
Information about urinary culture results and feasibility to participate in the trial			x			
**Informed consent and randomization:**						
Signature informed consent				x		
Randomization allocation				x		
**Interventions:**						
Dispensation of study medication				x		
Transurethral intervention (ureteral stent manipulation)				x (+ 4–6 h)		
**Assessments:**						
Patient history, physical exam, pregnancy test		x				
Ureteral stent discomfort questionnaire		x			x	x
Vital signs (temperature, blood pressure, heart rate, and respiratory rate)		x		x	x	x
Blood draw for analyses: sodium, potassium, creatinine, eGFR (CKD-EPI), complete blood count		x^a^		x^b^	x	x^c^
Urine sampling for analyses: urine culture (microbiology)		x^a^		x^b^	x	x
**Assessment of anti-biofilm activity (secondary outcome)**				x		
Blood draw for analyses: aminoglycoside + mannitol level (AMK/Man level) at 1, 3, and 6 h after administration of drug				x		
Urine sampling for analyses: ceftriaxone, mannitol, and aminoglycoside levels in urine				x (during intervention)	x	
**Assessment of post-interventional clinical UTIs (primary outcome)**					x	X

^a^By phone

^b^Blood draw at 1/3/6 h post-infusion; urine culture intraoperatively

^c^Only if abnormal values at V2

### Study procedures

Patients with ureteral stents will undergo evaluation in the pre-surgical outpatient clinic, typically 2 weeks before endourological interventions, to assess laboratory and for urine culture. Following informed consent and a 24-h reflection period, patients qualifying for the trial based on urine culture results (see study population) will be randomly assigned to one of three antibiotic treatment arms (Fig. 1) at visit 1. The randomization list, maintained in the Pharmacy unit, will assign patient identification and randomization numbers to treatment infusion bags. The principal investigator will receive sealed envelopes for emergency unblinding to ensure confidentiality. Antibiotic prophylaxis, delivered as a single infusion over 30 min, will commence immediately upon receipt from the hospital pharmacy.

### Study intervention/allocation to blind treatment

The study will employ a pre-defined allocation table with balanced 1:1:1 to ensure equitable participant distribution, generated by the clinical research unit of the CHUV Pharmacy according to their standard process. The preparation of the study drug will be carried out by the unblinded pharmacist investigators. The intervention will consist in a single infusion over 30 min. The three treatment groups are:Amikacin (low dose) + mannitol (arm 1): aminoglycosides (amikacin 500 mg, approximately 7.5 mg/kg; potentiated with mannitol 5 g). Thus, this combination therapy of aminoglycosides and mannitol reduces toxicity by decreasing the aminoglycoside dosing (potentiation of the activity of aminoglycosides by mannitol).Amikacin (arm 2): a standard of antibiotic prophylaxis for endourological treatments (ureteroscopies, TURP, etc.). The dosage of 1000 mg is standard dosing for the average adult weight (ca. 15 mg/kg) [11, 22], a first-line treatment for urinary tract infections in Australia (*sahealth.sa.gov.au*).Ceftriaxone (arm 3): a standard of care antibiotic prophylaxis in Switzerland. In clinical practice in Switzerland, asymptomatic bacteriuria is generally treated by antibiotics as recommended by IDSA guidelines [7]. The dosage of 2 g intravenously reflects the general practice.

### Criteria for discontinuation/modifying allocated intervention

As the intervention is a single infusion, discontinuation criteria do not apply.

### Relevant concomitant care permitted or prohibited

No antibiotics are allowed (exclusion criteria) immediately prior to or during the trial.

### Provisions for post-trial care

Additional lab parameters to monitor nephrotoxicity or tonometry for suspected ototoxicity will be made available to participants displaying adverse events in the context of the trial.

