### Study endpoints

The primary outcome is the rate of postoperative infections 48 h postoperatively. Postoperative infections include systemic symptoms and positive urine/blood cultures matching preoperative urine cultures as deemed by the adjudication committee. Secondary outcomes include microbiological eradication via anti-biofilm activity assessed through catheter sonication, quantitative culture, and intraoperative urine culture; sustained microbiological eradication measured by urine cultures at postoperative days 2 and 14; and primary pharmacokinetic parameters of mannitol and antibiotics in blood and urine samples at specified time points. Safety outcomes will include monitoring the incidence of adverse events related to amikacin/mannitol combination therapy throughout the study, including serious adverse events (SAEs) and pre-specified adverse events of special interest such as ototoxicity and nephrotoxicity, along with vital signs. Additionally, postoperative complications at day 14 will be assessed using the Clavien-Dindo classification [19].

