### Study procedures/participant timeline (Table 2)

During the screening visit (V0), patients with ureteral stents planned for endourological manipulation are preselected based on chart reviews every 2–4 weeks. A urine culture is taken as part of standard care. Written informed consent is obtained after a minimum 24-h reflection period, either on the day of intervention (for day-surgery) or the day before surgical intervention for pre-hospitalization, with results documented in both a screening log and the (eCRF). During visit 1 (V1), patients consenting to the study will undergo eligibility assessment by the investigator, followed by randomization conducted by pharmacy research staff. Data collected during the visit will be recorded in the eCRF, and patients will receive study treatment from the pharmacy as a single infusion bag, administered within 30 min of delivery, with intraoperative urine cultures and hardware extraction for culture, along with blood and urine samples for pharmacokinetic and antibiotic concentration quantitation. During visit 2 (V2), occurring 2 days post-intervention, patient history will be obtained regarding infectious complications; adverse events will be assessed and managed. Urine cultures and samples for antibiotic and mannitol analysis will be obtained, along with blood for safety laboratory assessments including electrolytes and creatinine, with all data recorded in the eCRF by research staff. During the end of study visit (V3), occurring 14 days post-intervention, patient history will be obtained regarding infectious complications, and adverse events will be assessed and managed. Urine cultures will be obtained, and blood may be drawn for safety laboratory assessments if deemed necessary based on pathological results from V2, with all data recorded in the eCRF by research staff.

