The potentiation of existing antibiotics represents a new and promising approach to circumventing bottlenecks of antibiotics development [14]. In addition, the combination of aminoglycosides with mannitol, as used here in the UROPOT trial, has the great advantage that the oto- and nephroprotective effect of mannitol can be utilized. On the one hand, the low dosage reduces potential side effects and toxicity of aminoglycosides, and on the other hand, mannitol seems to provide additional direct protection [15]. In addition to the effect of biofilm eradication, as demonstrated in preclinical models, the combination thus represents a unique protective and effective drug interaction which is the backbone of the UROPOT trial. UROPOT is already running at the Urology Outpatient clinic of CHUV.

A potential challenge in the UROPOT trial is achieving effective concentrations of amikacin and mannitol in the urinary tract for a sufficient period. Our current schedule may not allow a sufficient exposure for maximal effect to take place. To address this issue, bacterial strains derived from patients will be characterized in biomimetics for kinetics of potentiation within our consortium ([name]). This should identify potential strains refractory to potentiation and better calibrate dosing of antibiotics and metabolites in the urinary tract.

Logistically, the UROPOT trial does not face significant challenges as a single intervention is performed with 14-day follow-up consistent with standard of care. Adherence to treatment protocols is therefore simple and additional visits are straightforward. There is limited data collection and analysis, which should also make addressing potential safety concerns associated with the investigational therapy straightforward.

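### Ototoxicity is an adverse event of special interest, but the only test named for suspected cases is tonometry, and no pre-dose hearing status is specified for comparison

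*Protocol article*

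**What the plan says.** In the protocol article, Study endpoints places ototoxicity within the safety outcomes, as one of the "pre-specified adverse events of special interest such as ototoxicity and nephrotoxicity, along with vital signs".

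Provisions for post-trial care describes the extra work-up for participants with adverse events: further laboratory parameters for nephrotoxicity and, for hearing, "tonometry for suspected ototoxicity will be made available to participants displaying adverse events in the context of the trial". No other test for ototoxicity is named anywhere in the article.

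The places that bear on hearing before and after dosing are:

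- **Eligibility (Table 1, exclusion 4).** "Middle to severe hearing impairment" excludes a patient. Table 2 schedules the criteria check at visits 0 and 1.
- **Clinical baseline (Table 2).** "Patient history, physical exam, pregnancy test" is marked at visit 0 only.
- **Follow-up (Study procedures/participant timeline).** At visit 3, "patient history will be obtained regarding infectious complications, and adverse events will be assessed and managed". The text for visit 2 is equivalent.

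Reduced toxicity is part of the case for the combination arm. Study intervention/allocation to blind treatment says that the lower aminoglycoside dose reduces toxicity, and the Discussion adds that "the oto- and nephroprotective effect of mannitol can be utilized".

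**The concern.** Tonometry is a pressure measurement. It yields no hearing threshold and can neither support nor refute a suspicion of ototoxicity. The one sentence that says how such a suspicion would be examined therefore names the wrong kind of test.

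The rest of the article does not make up for this. It names no instrument for hearing, specifies no recorded hearing status before the infusion, and does not say what makes a hearing complaint new. The safety outcome most closely tied to the aminoglycoside dose would then rest on symptoms reported at visits 2 and 3, with nothing specified to compare them with.

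What is at stake is how a low count would be read. The Sample size section justifies 30 patients per group partly by the safety information they will provide. A report of few or no ototoxicity cases could be cited in favour of the low-dose combination although the measurement behind it was weak.

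**Working it through.** **Step 1. The two named events of special interest, side by side.**

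| | Nephrotoxicity | Ototoxicity |
|---|---|---|
| Status (Study endpoints) | Event of special interest | Event of special interest |
| Before dosing | Creatinine and eGFR at visit 0; eGFR limit in exclusion 3 | Exclusion 4, no method given; general history and examination at visit 0 |
| After dosing (Table 2) | Creatinine and eGFR on day 0 after infusion, at visit 2, and at visit 3 if visit 2 was abnormal | No hearing item shown |
| Adverse-event assessment at visits 2 and 3 | Yes | Yes |
| Extra work-up (Provisions for post-trial care) | Additional laboratory parameters | Tonometry |

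Nephrotoxicity has a baseline, an objective follow-up and a fitting work-up. Ototoxicity has an entry exclusion and general adverse-event assessment, and the work-up named for it does not fit.

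**Step 2. Baseline.** Exclusion 4 starts at a middle degree of impairment, so a patient with mild impairment may be randomized. The article does not say that such a status is recorded. A complaint on day 2 or day 14 could be compared with whatever the general history happened to note, but not with a specified pre-dose answer or measurement.

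**Step 3. What a zero count would show.** The article gives no ototoxicity rate, power or detection figure, so there is nothing to reproduce. The following is illustration only. The true rate p and the share s of true cases that the trial captures are both assumptions.

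Inputs: n = 30 per arm (Sample size), and n = 60 for the two arms that receive amikacin.

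Two-sided 95% upper limit on the captured rate when no case is seen: U = 1 − 0.025^(1/n).

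- n = 30: U = 1 − 0.025^(1/30) = 11.6%.
- n = 60: U = 1 − 0.025^(1/60) = 6.0%.

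These limits apply only to cases that are captured. If a share s is captured, the limit on the true rate is U/s. For n = 30 this is 0.1157/0.5 = 23.1% when half are captured, and 0.1157/0.2 = 57.9% when one in five is.

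Chance of seeing at least one case in an arm of 30: 1 − (1 − p·s)^30.

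| Assumed true rate p | s = 1 | s = 0.5 | s = 0.2 |
|---|---|---|---|
| 2% | 45.5% | 26.0% | 11.3% |
| 5% | 78.5% | 53.2% | 26.0% |
| 10% | 95.8% | 78.5% | 45.5% |

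Example: p = 5% and s = 0.5 give 1 − (1 − 0.025)^30 = 53.2%.

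The information in a zero count falls quickly as capture becomes incomplete, and the article gives no basis for judging how complete it would be.

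**The case against.** The strongest reply has four parts.

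**Adverse events are assessed.** Visits 2 and 3 both include adverse-event assessment, with data entered in the eCRF, and Study endpoints has adverse events monitored throughout the study. A reader might infer from Table 2 that ototoxicity cannot be detected at all, or comes to light only if a patient volunteers it. The article supports neither. Symptomatic hearing loss, tinnitus or vertigo can be recorded, and the article does not say whether events are asked about or only reported spontaneously. This part stands.

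**Table 2 is incomplete.** It has no adverse-event row, yet the timeline text places adverse-event assessment at visits 2 and 3. The absence of a hearing row is therefore weak evidence that hearing is never assessed, and the full protocol, which is not shown, may contain more. This also stands. The weight of the point lies on the sentence that names tonometry, which is a statement and not a silence.

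**The word may be a slip.** It could be a translation or drafting error for a hearing test, and the sentence sits in a care provision, not in an endpoint definition. That is possible, and the article cannot settle it. It bears on what sites actually do, but the published text needs correcting either way.

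**Events are expected to be rare, and no between-arm test of ototoxicity is described.** Oversight and monitoring expects such events to be very infrequent after a single dose, so a low count may be accurate. A reader might infer that the count will be near zero whatever the truth. The table above does not bear that out: at a true rate of 10%, at least one case in 30 would be seen with probability 78.5% at half capture and 45.5% at one-in-five capture. What remains is that a low count could not be clearly separated from incomplete capture.

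**Conclusion.** The point holds in a limited form. An event of special interest is paired with a test that does not measure hearing, and the published schedule shows neither a hearing test nor a hearing question on either side of dosing. Symptomatic cases can still be recorded and hearing is considered at entry. No baseline hearing status is specified for comparison, and no valid confirmatory test is named.

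The consequence is for interpretation: a low ototoxicity count would be weak support for the claim of reduced toxicity. How weak depends on the unknown capture share. With zero cases in 30 patients, the upper limit on the true rate is 11.6% at full capture and 23.1% at half capture. These figures rest on assumed capture shares and on nothing in the article.

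The primary outcome is not affected. The correction is worth making because reduced toxicity is central to the rationale and the change is small.

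**What to change.** 1. **Correct the named test.** Reconcile Provisions for post-trial care with Study endpoints and Table 2 by replacing tonometry with a hearing test (audiometry), still for suspected cases only. If the full protocol already names a hearing test, an erratum to the article is enough.
2. **Add a short fixed set of questions** on hearing, tinnitus and balance before dosing (visit 0, or visit 1 ahead of the infusion) and at visits 2 and 3. Ask them in the same words in all three arms by staff blinded to allocation. The ceftriaxone arm then shows the background level of such complaints without an aminoglycoside.
3. **Define the count.** Count ototoxicity as a new or worsened answer against the pre-dose answers, and report audiometry results for suspected cases alongside.

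The cost is a minor amendment and about a minute per visit. No visit is added, and patients already complete the "Ureteral stent discomfort questionnaire" at visits 0, 2 and 3. The downside is that fixed questions will bring in more unspecific complaints. Comparison with the pre-dose answers and with the ceftriaxone arm helps to put these in context.

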### Study endpoints

The primary outcome is the rate of postoperative infections 48 h postoperatively. Postoperative infections include systemic symptoms and positive urine/blood cultures matching preoperative urine cultures as deemed by the adjudication committee. Secondary outcomes include microbiological eradication via anti-biofilm activity assessed through catheter sonication, quantitative culture, and intraoperative urine culture; sustained microbiological eradication measured by urine cultures at postoperative days 2 and 14; and primary pharmacokinetic parameters of mannitol and antibiotics in blood and urine samples at specified time points. Safety outcomes will include monitoring the incidence of adverse events related to amikacin/mannitol combination therapy throughout the study, including serious adverse events (SAEs) and pre-specified adverse events of special interest such as ototoxicity and nephrotoxicity, along with vital signs. Additionally, postoperative complications at day 14 will be assessed using the Clavien-Dindo classification [19].

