Biofilm-associated bacteria exhibit “antibiotic tolerance,” and thus survive otherwise lethal doses of antibiotics, highlighting the need for effective strategies. While quinolones have an anti-biofilm activity, resistance in Enterobacteriaceae like *E. coli* or *K. pneumoniae* approaches 20% in Switzerland (*anresis.ch*), limiting their utility in urinary tract infection management. Addressing the lack of biofilm eradication strategies, rising antibiotic resistance, and the steady increase in endourological interventions following previous ureteral stenting, the UROPOT study aims to evaluate the clinical significance of a novel antimicrobial strategy during mucosal lesion-inducing procedures in pre-stented patients with asymptomatic bacteriuria.

Previous research in a murine catheter-associated urinary tract infection (CAUTI) model has demonstrated that metabolic stimulation by substrates such as mannitol can enhance the efficacy of aminoglycosides in killing *E. coli*, including tolerant forms like biofilms [13, 14]. Moreover, the potentiation allows a reduction of aminoglycoside dosing [15]. Amikacin and mannitol are both approved for clinical use but exhibit differing safety profiles. Aminoglycosides such as amikacin can cause dose-dependent ototoxicity and nephrotoxicity [16]. In contrast, mannitol is used without major side effects and is not metabolized by host cells, being fully excreted by the kidneys. Pharmacological data suggest that low systemic doses of aminoglycosides achieve urine concentrations far exceeding the Clinical and Laboratory Standards Institute breakpoint for Enterobacteriaceae, and a single dose can sustain therapeutic levels against pathogens like *E. coli* for up to 3 days, making it a promising outpatient option [17, 18].

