### Statistical analysis

The primary outcome is the proportion of postoperative infections within 48 h postoperatively. Fisher’s exact test will applied to compare the proportions between mannitol + low-dose amikacin arm vs full-dose amikacin arm and mannitol + low-dose amikacin arm vs ceftriaxone arm, respectively. To account for multiple comparisons, single-step method will be applied to control the family-wise error rate. Odds ratios with 95% confidence intervals and associated *p* value will be reported. Due to its exploratory nature and limited number of participants, no interim analysis will be performed. Microbiological eradication will be compared between the same groups mentioned in the primary analysis using *t*-tests. Difference in means with 95% confidence intervals and *p* values will be reported. If normality assumption is not met and the data approximately follow a log-normal distribution, data will be log-transformed before applying *t*-tests. In this case ratios of geometric means with 95% confidence intervals and *p* value will be reported. If none of the above methods hold, non-parametric methods will be considered.

Sustained microbiological eradication will be analyzed using mixed-effects models to account for the repeated measurements. Fixed effects will be the baseline microbiological eradication measured at D0, the intervention, the visit (D2 and D14), and the interaction between the intervention and the visit. Subject-specific random effect will be considered. Statistical assumptions will be assessed, and a similar methodology will be applied as for microbiological eradication to addressed them.

Primary pharmacokinetic parameters in blood (Cmax, AUC, t1/2) will be calculated for mannitol, amikacin, ceftriaxone, and for each intervention arm. In urine, descriptive statistics will be reported without any specific comparisons and spot urine concentrations.

Planned analyses will adhere to the sections detailing primary, secondary, and safety analyses, with a statistical analysis plan finalized and signed by all parties before code break. Datasets for analysis include the intention-to-treat (ITT), per-protocol (PP), and safety populations, with primary and secondary outcomes assessed in the ITT population and safety outcomes analyzed in the safety population.

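### The day-2 urine culture falls in the period when, on the protocol's own figure, amikacin may still be active; day 14 should carry sustained eradication, with a rule for non-study antibiotics

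*Protocol article*

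**What the plan says.** Under Study endpoints, the secondary outcome is "sustained microbiological eradication measured by urine cultures at postoperative days 2 and 14", with neither day given priority. Table 2 sets visit 2 at day 2 ± 24 h and visit 3 at day 14 ± 4 days. It places the procedure 4–6 h into day 0, the day on which study drug is given as a single infusion.

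Under Statistical analysis, both visits enter one mixed-effects model. Its fixed effects are the day-0 baseline, arm, visit and the arm-by-visit interaction. The text does not say which visit's contrast answers the question of sustained eradication.

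On how long the drug lasts, Background and rationale states that "a single dose can sustain therapeutic levels against pathogens like *E. coli* for up to 3 days". The sentence opens with a hedge: "Pharmacological data suggest that low systemic doses of aminoglycosides achieve urine concentrations far exceeding the Clinical and Laboratory Standards Institute breakpoint". The Discussion is more cautious about the regimen: "Our current schedule may not allow a sufficient exposure for maximal effect to take place". No duration is given for ceftriaxone. Table 2 lists "Urine sampling for analyses: ceftriaxone, mannitol, and aminoglycoside levels in urine" during the procedure and again at visit 2; the analysis section uses these levels descriptively only.

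On other antibiotics, the concomitant-care section says "No antibiotics are allowed (exclusion criteria) immediately prior to or during the trial". The participant timeline says that infectious complications are asked about at visits 2 and 3 and that adverse events are dealt with there. It does not say how. On analysis sets: "Datasets for analysis include the intention-to-treat (ITT), per-protocol (PP), and safety populations". Primary and secondary outcomes are assigned to the ITT population.

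**The concern.** Sustained eradication should mean that the organism stays away once the drug has gone. If drug may still be present at an active concentration when urine is sampled, a negative culture has two explanations that the culture alone cannot separate: the organism was eliminated, or it was suppressed. The arms receive amikacin 500 mg with mannitol, amikacin 1000 mg, or ceftriaxone 2 g, so residual drug at visit 2 may differ between them and enter the day-2 contrasts.

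Day 14 raises a different question. If a patient develops an infection and receives a non-study antibiotic active against the organism, a sterile day-14 culture reflects that treatment. Taken as observed, it counts as eradication under the allocated arm, and the arm with more infections collects more such credits.

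A conflict in the text makes this harder to handle. Antibiotics are barred during a trial whose primary outcome is infection and whose follow-up runs to day 14. Read literally, any antibiotic given for a primary event is prohibited medication. The analysis then has no clear basis for deciding how those patients count.

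**Working it through.** The protocol states no figure for this endpoint that could be reproduced, and 30 per group is a feasibility number. The check compares the visit windows with the stated drug duration, then sizes the day-14 effect under assumed rates.

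**Day 2 against the 3-day figure.** Inputs: upper bound 3 days = 72 h (Background and rationale); visit 2 at 48 ± 24 h and procedure at +4–6 h (Table 2). I take the 4–6 h as counted from study drug.

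- Counted from day 0: 48 − 24 = 24 h to 48 + 24 = 72 h. Share within 72 h: (72 − 24)/48 = 100%.
- Counted from the procedure, 4 h lag: 28–76 h after drug, nominal 52 h. Share: (72 − 28)/48 = 91.7%.
- Counted from the procedure, 6 h lag: 30–78 h after drug, nominal 54 h. Share: (72 − 30)/48 = 87.5%.

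The nominal visit time is inside the bound on every count.

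**Day 14 against the same figure.** (14 − 4) × 24 = 240 h and (14 + 4) × 24 = 432 h. The earliest visit is more than three times the 72 h bound, so residual study drug is not an issue.

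**Non-study antibiotics at day 14.** Only patients treated for infection are affected. At an assumed 5–30% of 30 per arm, that is 1.5–9 patients, leaving 70–95% of cultures untouched.

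To size the effect on a contrast, treat eradication as yes/no and write

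observed eradication = e + r × c,

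where e is eradication by study drug alone, r the proportion infected and treated, and c the proportion of those cleared by the other antibiotic. Infected patients are assumed otherwise positive. With e = 60% and 40% in arms A and B (true difference 20 points) and c = 80% or 90%, all assumed:

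| r in A | r in B | Observed difference, c = 80% | c = 90% |
|---|---|---|---|
| 10% | 10% | 68 − 48 = 20 | 69 − 49 = 20 |
| 5% | 15% | 64 − 52 = 12 | 64.5 − 53.5 = 11 |
| 10% | 30% | 68 − 64 = 4 | 69 − 67 = 2 |
| 5% | 30% | 64 − 64 = 0 | 64.5 − 67 = −2.5 |

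The distortion is (r in A − r in B) × c. It vanishes when infection rates are equal and otherwise moves the contrast towards the arm with more infections.

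**The case against.** The best defence of day 2 is that the 3-day figure is hedged and is a maximum. It comes from sources not shown here, and the Discussion doubts that exposure is long enough for maximal effect. That stands: carry-over at visit 2 is possible, not demonstrated. It does not remove the ambiguity, because the Background uses the same figure to support the approach and nothing in the analysis separates suppression from eradication.

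A second defence is that the tools are already there. The arm-by-visit interaction makes the day-14 contrast separately estimable, and urine levels are collected at visit 2. This is right and makes the change cheap, but the text still gives both days the same label.

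A third is that handling of antibiotics after study drug is ordinary SAP content and that the SAP is not shown. Also right: the missing rule is not itself a fault. What the article does contain is a bar on antibiotics that sits badly with its own primary endpoint. The bar refers to the exclusion criteria and may have been meant for antibiotics before randomization or added to the prophylaxis, but its wording extends to the whole trial.

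A reader might infer more than the document supports:

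- *That neither visit measures eradication.* Day 14 is clear of study drug, and only treated patients are affected there.
- *That day 2 is biased towards amikacin against ceftriaxone.* Silence about ceftriaxone does not show shorter persistence, and one of the two planned contrasts is amikacin against amikacin, with the higher dose in the comparator.
- *That carry-over removes amikacin-arm events from the primary outcome.* Study endpoints joins symptoms and positive cultures, but the Abstract and Objectives allow either. Drug in urine that prevents infection is also what prophylaxis is for.
- *That the per-protocol set loses its primary events.* The article neither defines that set nor says that treated patients leave it, and the main analyses are ITT.

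**Conclusion.** The point holds in a limited form. On the protocol's own upper bound, 88–100% of the visit 2 window falls while amikacin may still be active in urine, so a negative day-2 culture is weak evidence of sustained eradication. Differential carry-over between the two amikacin doses and ceftriaxone is possible, in an unknown direction.

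Day 14 is a usable measure. Its weakness is confined to patients given an active non-study antibiotic. That such treatment occurs is likely but not written. The bias is zero with equal infection rates. In the illustration it took a 20-point difference to 11–12 points at 5% versus 15% infection and to 2–4 points at 10% versus 30%. Those rates, the clearance of 80–90% and the yes/no outcome are assumptions, so these figures show a mechanism and are not a forecast for this trial.

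The bar on antibiotics during the trial does need reconciling with the infection endpoint. All of this concerns a secondary outcome of an exploratory trial, but it can be settled before code break at little cost.

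**What to change.** 1. Name the day-14 arm contrast from the planned mixed model as the estimate of sustained eradication. Report day 2 as supportive, labelled as possible on-drug suppression, beside the visit 2 urine drug levels already collected.
2. Record the start date of any non-study antibiotic. For day 14, classify patients who received one active against the index organism as not eradicated by study drug, and give the as-observed analysis as sensitivity. If the modelled outcome is a quantitative count, state the equivalent rule on that scale.
3. Reconcile the concomitant-care statement with the infection primary endpoint and with the timeline's statement that adverse events are dealt with at visits 2 and 3. Which clinical rule applies is for the sponsor to decide.
4. State that a primary-outcome event and its management do not by themselves exclude a patient from the per-protocol set.

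Cost: wording in the protocol and SAP and one added eCRF date field. The price is that day-2 data become supportive.
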